We performed an extensive search in the PubMed, Web of Science, and PEDro databases and found only one pilot study [11] which compared the effectiveness of the NWFP to improve mobility of pre-frail elderly people. The participants were randomized to one of three groups: (1) control, (2) seated exercise (traditional senior fitness program), or (3) NWFP group (basic games and addition of weight vest with 2% of their body weight every 2 weeks). The training of groups 2 and 3 was performed for 45 min, three times a week, for 15 weeks. There was improvement in physical functional status in the seated exercise and NWFP group compared to the control group. Despite the positive effects of the NWFP group, there were some methodological issues in this pilot study such as the absence of blindness of the subjects, therapists, and evaluators and the absence of the intention-to-treat analysis, since there was a dropout of 12 participants during the study. Furthermore, this pilot study did not assess the feasibility, safety, or acceptability of the NWFP for pre-frail elderly people. Finally, the participants of the NWFP group performed their training using a weight vest. The addition of weight certainly interfered in the intensity of the intervention with the games. In fact, the weight addition makes it difficult to infer whether the improvement occurred due to training with the games or the resistance of the weight vest.

Despite evidence of the positive effects of IVGs on clinical outcomes of community dwelling elderly people [12–20], it is not clear whether IVGs are feasible, safe, and acceptable for frail elderly people. Furthermore, the effectiveness of IVGs on this population has not been established.

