### Trial design

The study will be a randomized controlled, parallel group, feasibility trial. Participants will be randomly assigned 1:1 to NWFP training or usual care. Study assessments will be conducted before and after the intervention and 30 days after the end of the intervention (follow-up).

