### Sample size

As this is a feasibility study, no formal sample size calculation was performed [35]. Instead, this study follows sample size recommendations for pilot randomized controlled trials [36] and aims to have at least 12 participants per group who provide full data. We aim to recruit 15 participants for each group (i.e., total sample size of 30) to compensate for a 20% dropout. This number of participants is deemed adequate to provide sufficient information on key feasibility issues such as recruitment and acceptability of the intervention.

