### Statistical analyses

A detailed analysis plan will be prepared before all the data has been collected. Analyses will be conducted in Dell™ Statistica (version 13.0) using the principles of intention-to-treat. Descriptive statistics will be used to characterize the groups at baseline and present the feasibility outcomes. Although determining differences in clinical outcomes between the two groups is not the primary purpose of this trial, comparisons will be undertaken to investigate the feasibility of studying these outcomes and calculate estimates for the likely effect sizes and 95% confidence intervals. The effect size will be calculated in order to determine whether change can be detected over time using these outcome measures and to determine the most appropriate primary outcome. The focus of the results will be on the estimates of the treatment effects rather than statistical significance, and as such, no hypothesis testing will be undertaken [37]. Differences between the two comparison groups will be presented in the form of an unadjusted mean difference for continuous outcomes with their associated 95% confidence intervals.

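### The only between-group estimator fixed is an unadjusted mean difference, although baseline values and a frailty stratum are available and 20% dropout is expected

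*Protocol article*

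**What the plan says.** All references are to the protocol article.

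- **Statistical analyses.** Analyses are to be run "using the principles of intention-to-treat". For the clinical outcomes, "Differences between the two comparison groups will be presented in the form of an unadjusted mean difference for continuous outcomes", with 95% confidence intervals. No other between-group estimator is named. No hypothesis tests are planned. The effect sizes are to help choose the primary outcome for a later trial. The section also announces a fuller plan: "A detailed analysis plan will be prepared before all the data has been collected".
- **Sample size.** The trial "aims to have at least 12 participants per group who provide full data", and "We aim to recruit 15 participants for each group (i.e., total sample size of 30) to compensate for a 20% dropout".
- **Trial design and Participant timeline.** Participants are assessed before the intervention, after it, and 30 days after it ends.
- **Randomization.** Allocation is 1:1, stratified by pre-frail and frail status.

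**The concern.** An unadjusted difference in means, taken on observed values, compares whoever was measured. It uses neither the baseline of those who were lost nor the stratum used in the randomisation. Recruiting 15 per group to finish with 12 restores the number analysed. It does not restore comparability if the people lost differ between arms.

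Such a difference is possible, though not shown. One arm is asked to attend 14 supervised sessions of 50 minutes, and the other receives verbal guidance and a booklet (Intervention).

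What is at stake is the set of effect sizes carried to the main trial. The shift depends on how strongly each outcome correlates with whatever drives loss. It therefore need not be the same for all six clinical outcomes, and could affect their ranking when the primary outcome is chosen.

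**Working it through.** **The plan's own figure.** 12 / (1 − 0.20) = 15 per group, 30 in total. This reproduces the Sample size section.

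**Inputs from the document.** 20% dropout; 12 per group with full data; 1:1 allocation; unadjusted mean difference with 95% interval.

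**Assumptions not in the document.** Outcome and baseline are normal with SD 1, scored so that higher is better. The true effect is zero. The baseline-outcome correlation r is 0.3, 0.5 or 0.7. The patterns of loss are those listed below.

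**Strong dependence on baseline in the game arm, random loss in controls.** Removing the lowest 20% at baseline raises the retained baseline mean by φ(z₀.₂₀)/0.80 = 0.350 SD. The outcome mean rises by r × 0.350, which gives 0.105, 0.175 and 0.245 SD.

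**Simulation (1,000,000 per arm, 20% lost in each arm).** The adjusted column is a linear model with baseline as covariate, fitted to observed cases.

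| Loss in game arm (controls random unless stated) | r | Unadjusted shift, SD | Baseline-adjusted shift, SD |
|---|---|---|---|
| Random in both arms | 0.3–0.7 | 0.00 | 0.00 |
| Lowest 20% at baseline, both arms | 0.3–0.7 | 0.00 | 0.00 |
| Moderate: logistic, log odds of loss 1 higher per SD lower baseline | 0.3 / 0.5 / 0.7 | 0.05 / 0.09 / 0.12 | 0.00 |
| Strong: lowest 20% at baseline | 0.3 / 0.5 / 0.7 | 0.10 / 0.17 / 0.24 | 0.00 |
| Extreme: lowest 20% on the unseen outcome itself | 0.3 / 0.5 / 0.7 | 0.35 / 0.35 / 0.35 | 0.32 / 0.28 / 0.20 |

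Positive values favour the games.

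**If change from baseline is compared instead.** With equal SDs at both visits, the shift in change is r × 0.350 − 0.350 = −(1 − r) × 0.350. Under strong dependence this is −0.245, −0.175 and −0.105 SD at r = 0.3, 0.5 and 0.7, so the direction is against the games. Under moderate dependence the retained baseline mean rises by about 0.086/0.5 = 0.17 SD, and the change shifts by about −0.12, −0.09 and −0.05 SD.

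**Scale.** The 95% half-width is t(0.975, 2n − 2) × √(2/n). With 12 per arm it is 2.074 × 0.408 = 0.85 SD. With 15 per arm it is 2.048 × 0.365 = 0.75 SD.

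**The case against.** A reader might go further and infer that the plan breaks its own intention-to-treat promise, or that it fixes a complete-case analysis at each visit. The Background section does fault an earlier pilot for "the absence of the intention-to-treat analysis, since there was a dropout of 12 participants during the study", which makes the inference tempting. The text does not support it:

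- Unadjusted means without covariates. The section does not say that participants without a value are left out, and an unadjusted difference can be computed after imputation.
- How missing values are handled is commonly left to the analysis plan, which the same section announces. Its absence from a condensed article is not an error.
- Linking intention-to-treat to dropout in the Background suggests, if anything, an intention to include those who drop out.

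Nor can a direction be asserted. A shift towards the games needs selective loss in the game arm and a comparison of visit values. Weaker controls could leave instead. Change may also be what is compared: the Clinical outcomes section judges change against 3.5 and 4.2 points, and the Statistical analyses section speaks of detecting change over time. Nothing in the document indicates differential loss, since the same 20% is allowed for each group.

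The consequence is also limited. The trial estimates without testing, between-group differences are not its primary purpose, and the interval is much wider than any plausible shift.

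All of this stands. It does not reach the narrower point. The unadjusted estimator is stated, not left open, and it is the weaker choice when baseline and stratum are already recorded.

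**Conclusion.** The point holds as a recommendation to replace a stated estimator, not as a contradiction in the plan. If the unadjusted difference is taken on observed values, baseline-related loss that differs between arms shifts it by about 0.05 to 0.12 SD (moderate) or 0.10 to 0.24 SD (strong) when visit values are compared, and by similar amounts in the opposite direction when change scores are compared. Random loss, or the same loss in both arms, causes no shift, so the 20% dropout alone is not a source of bias.

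These sizes rest on assumed correlations and loss mechanisms. Adjusting for baseline brings the shift to about zero when loss depends only on baseline and the relation is linear. It does much less when loss depends on the unseen outcome: 0.20 to 0.32 SD remains of 0.35 SD, so that extreme case should not be counted as a benefit of the change.

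**What to change.** In the Statistical analyses section, replace the unadjusted mean difference with an arm difference adjusted for the baseline value of the outcome and for frailty stratum, reported with its 95% interval at post and at follow-up. Either of two forms would do:

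- a linear model at each of the two times, with baseline value and stratum as covariates; or
- one repeated-measures mixed model per outcome, using all randomised participants with at least one assessment, analysed in the allocated arm.

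Keep the unadjusted difference as a secondary description. With baseline as a covariate in the linear model, analysing visit values or change scores gives the same arm difference, so the open question of which is compared no longer matters for the main estimate.

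The cost is wording and a little modelling; no new data are needed. The Trial status section reports about half the participants recruited and the detailed plan is described as still to be prepared, so the change can be made there, and should be recorded before outcomes are compared by arm. The downsides are a model fitted in 24 to 30 people and a missing-at-random assumption. Bias from loss that depends on unseen outcomes largely remains. The calculations above cover the baseline-adjusted linear model; the mixed model was not simulated.

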### Adverse events

An adverse event is defined as any untoward medical occurrence in a participant which does not necessarily have a causal relationship with this intervention. Any adverse events will be reviewed by the study team, and likely causality will be assessed and reported on a form.

### Auditing

We will institute a rigorous program of quality control. The research sponsor in conjunction with the trial coordinator will be responsible for ensuring adherence to the trial protocols at the trial sites. Quality assurance checks will be undertaken by the University of Sao Paulo to ensure integrity of randomization, study entry procedures, and data collection.

### Protocol amendments

Any modifications to the protocol which may impact on the conduct of the study, potential benefits to the patient, or may affect patient safety, including changes in study objectives, study design, patient population, sample sizes, study procedures, or significant administrative aspects will require a formal amendment to the protocol. Such amendments will be agreed upon by the Ethics Committee of the Medical School of the University of Sao Paulo, Brazil, and the Brazilian Registry of Clinical Trials prior to implementation and notified to the health authorities in accordance with local regulations.

### Dissemination policies

The dissemination will be to inform a wide range of local, national, and international audiences about the results and conclusions. It must, however, be remembered as part of this strategy that the current project is preliminary work aimed at informing a subsequent definitive clinical trial. We aim to publish our research in journals that cover the relevant medical specialties and with preference for those that deposit publications in open access databases to increase free dissemination. In addition, we aim to present this research at appropriate national and international conferences.

## Discussion

The current study is designed to evaluate the feasibility, safety, acceptability, and functional outcomes of playing NWFP for frail older adults. This feasibility study is in preparation for a main trial that will go ahead if all feasibility criteria and hypothesis are met.

Frailty affects functionality in different aspects, such as mobility, gait, balance, muscle strength, motor processing, cognition, nutrition, and physical activity [38]. Due to the deficiencies in multiple systems, studies have shown that multimodal interventions including motor-cognitive stimulation can improve the mobility of frail elderly adults [39]. IVGs, among them the NWFP, are considered as a multimodal motor-cognitive intervention that can potentially improve motor and cognitive functions in the frail elderly. The NWFP can promote physical activity and improve balance, mobility, gait speed, muscle strength, flexibility, and functional abilities in older adults [40]. However, there is still no evidence in the literature that proves the feasibility, safety, acceptability, and functional outcomes of this intervention in frail elderly adults. We speculate that due to the challenging stimulation to the postural control and cognitive systems, added to factors that can improve motor learning such as visual and auditory feedback and motivating environment, the NWFP will be feasible, safe, and acceptable and will promote clinical benefit in frail elderly adults.

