### Hypotheses

We speculate that the frail elderly adults will improve their performance in the games and increase their scores;We hypothesize that the intervention based on the NWFP games will not cause any adverse events such as syncope, dizziness, vertigo, falls, or any other medical condition that requires hospitalization or leads to disability. A previous study [24] showed that elderly individuals with Parkinson’s disease presented good acceptability to training with the NWFP;We expect that the NWFP games will be acceptable to frail elderly adults. Despite this population possibly not being familiar with this kind of technology, the NWFP games were developed for entertainment with attractive and motivating virtual environment and are easy to use. A previous study [12] showed that elderly adults demonstrated good acceptability to training with NWFP;The training sessions with the NWFP will provide improvement in postural control, gait, quality of life, cognition, and mood.

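### The rule for going on to the main trial includes hypotheses of no intervention-caused adverse events and of benefit in five domains, which an estimation-only study of 15 per group cannot reliably settle

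*Protocol article*

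**What the plan says.** The only progression rule in the protocol article is in the Discussion, which refers to "a main trial that will go ahead if all feasibility criteria and hypothesis are met".

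The Hypotheses section lists four statements: game scores will rise, there will be no harm from the intervention, the games will be acceptable, and there will be clinical benefit. The safety statement is that "the intervention based on the NWFP games will not cause any adverse events such as syncope, dizziness, vertigo, falls" and other listed events. The clinical statement is: "The training sessions with the NWFP will provide improvement in postural control, gait, quality of life, cognition, and mood". It gives neither a comparator nor a size of improvement.

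The Statistical analyses section says that "determining differences in clinical outcomes between the two groups is not the primary purpose of this trial" and that "no hypothesis testing will be undertaken". The planned output for continuous outcomes is an "unadjusted mean difference for continuous outcomes with their associated 95% confidence intervals".

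The Sample size section reports no formal calculation. The study "aims to have at least 12 participants per group who provide full data", recruits 15 per group, and is judged adequate for feasibility questions such as recruitment and acceptability.

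Under Outcome measures, attendance is the only item with a numerical feasibility criterion (above 50% for all sessions and an average above 80% per session). Safety is the proportion of participants with a related event or any serious event, with no limit attached. Change thresholds are given for two clinical scales only, and nothing ties them to progression.

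**The concern.** Because the rule says all, every hypothesis becomes a condition for the main trial. Two of those conditions ask for conclusions about harm and benefit. The sample size and analysis sections say, reasonably, that the study is not built to give such conclusions. The absence of hypothesis tests is not the fault; that is sound practice in a feasibility trial. The fault is a go/no-go rule that leans on what the rest of the plan declines to establish.

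The decision to proceed is a main product of a feasibility study. Followed literally, the rule can stop a worthwhile programme because of one related dizzy spell, or because one of five noisy estimates falls on the wrong side. It can also pass a programme with no benefit, or with a related-event risk well above zero. If the rule is not followed, the decision is made after the data are seen.

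**Working it through.** **The plan's own figure.** 12 participants with full data and 20% dropout: 12 / (1 − 0.20) = 15 per group, 30 in total. This reproduces exactly.

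**Inputs.** From the protocol: 15 allocated to training, 12 expected with full data, 1:1 allocation, five named domains, mean differences with 95% confidence intervals. Assumed, because the protocol gives none: the per-person risk of an intervention-caused event, the true standardised effect d, and the correlation between the five outcomes. Each is shown as a range.

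**Safety condition.** The chance of no related event in n treated people is (1 − p)^n.

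| Assumed attributable risk p | n = 15 | n = 12 |
|---|---|---|
| 1% | 86% | 89% |
| 5% | 46% | 54% |
| 10% | 21% | 28% |
| 20% | 3.5% | 6.9% |

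The exact (Clopper-Pearson) two-sided 95% upper limit after zero events is 1 − 0.025^(1/n). For 0/15 this is 21.8%; for 0/12 it is 26.5%. Meeting the condition therefore does not exclude a related-event risk of about one in five.

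**Clinical condition, read as a between-group difference.** The 95% confidence interval half-width in SD units is t(0.975; 2n − 2) × √(2/n).

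- n = 15: 2.048 × √(2/15) = 0.75 SD.
- n = 12, with 22 degrees of freedom: 0.85 SD.

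For all five domains together, I simulated five equally correlated normal estimates, each with standardised mean d × √(n/2) (400,000 draws, n = 15 per group). The last column uses a critical value of 1.96; the t value of 2.048 makes it slightly smaller (3.7% instead of 4.6% to 4.7% at d = 0.5, correlation 0.5).

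| True effect | Correlation | All five estimates favourable | All five 95% CIs above zero |
|---|---|---|---|
| 0 | 0 | 3% | 0% |
| 0 | 0.5 | 17% | under 0.1% |
| 0.5 SD | 0 | 64% | 0.2% |
| 0.5 SD | 0.5 | 74% | 4.7% |
| 0.8 SD | 0 | 93% | 7% |
| 0.8 SD | 0.5 | 94% to 95% | 24% |

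With 12 per group and d = 0.5 SD, all five estimates are favourable in 56% to 68% of trials over the same correlations. At a correlation of 0.8 and 15 per group, the figures are 82% favourable at 0.5 SD, 29% with no effect, and 10% to 12% for all five intervals above zero at 0.5 SD.

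**Both conditions together.** Take direction-only benefit at d = 0.5 SD and correlation 0.5, and treat safety and benefit as independent. At 1% risk the joint chance is 0.86 × 0.74 = 0.64; at 10% risk it is 0.206 × 0.74 = 0.15. The result depends heavily on the assumed risk.

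**Clinical condition, read as within-group change.** These simulations do not apply to that reading. It has no decision rule either: thresholds exist for only the Mini-BEST-Test (3.5 points) and the FGA (4.2 points), and neither is linked to progression.

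**The case against.** A reader might infer that any adverse event at all would block the main trial, and that this makes the condition almost unreachable in frail people. The text does not support that. The hypothesis concerns events the intervention causes, and the Adverse events section separates occurrence from causality and has the study team assess the latter. The background rate of dizziness or falls is therefore the wrong rate to use. At a 1% attributable risk the condition would be met in 86% of trials; it fails more often than not only from about 5% upwards. What stands is that one related event breaches it, so the decision could turn on a single attribution.

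A reader might also take the rule as an only-if. The sentence says if, though no other route to the main trial is described.

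The strongest point is that hypotheses can be judged from estimates without tests, and the plan will produce mean differences, intervals and an event proportion. So there is no formal contradiction with the no-testing policy. That is right as far as it goes. But no rule says how those estimates would count, and the readings diverge sharply: direction only gives 64% to 74% at 0.5 SD, intervals above zero under 5%, for correlations of 0 to 0.5.

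Finally, this is one sentence in the Discussion. It changes no data collection, allocation or estimate, and the stated objectives can be reported in full whatever it says. That limits the severity but does not remove the problem.

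**Conclusion.** The point holds: the progression rule includes two hypotheses that a study of this size and purpose cannot reliably settle. Zero related events among 15 is neither a dependable gate nor evidence of safety. Favourable direction in all five domains misses a true moderate benefit in about 26% to 36% of trials and appears in 3% to 17% with no benefit. These clinical figures assume a between-group reading and correlations of 0 to 0.5; the safety figures depend on an attributable risk that the protocol does not give. It does not follow that the rule would usually stop the main trial, because that depends on the true risk and effects.

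This goes beyond detail that could be left to an analysis plan, since the article itself fixes both the conjunctive rule and the estimation-only purpose. Severity: should be fixed.

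**What to change.** - In the Discussion sentence, remove the reference to the hypotheses.
- Base progression on the attendance criteria already under Outcome measures, plus acceptability and safety criteria that the team fixes before outcome data are seen. Acceptability has to be named explicitly, or it drops out of the decision when the hypotheses are removed.
- Replace the zero-event condition with the observed proportion of participants with a related or serious event, judged against a limit that the team specifies in advance. Report the exact 95% confidence interval for information, but do not require it to lie below the limit: with 15 treated, even zero events gives an upper bound of 21.8%, so any lower limit could never be met.
- State that clinical-outcome estimates inform the design of the main trial, such as the choice of primary outcome, and do not enter the go/no-go decision.

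The cost is wording, the team's agreement on the two added criteria, and an amendment under the Protocol amendments section. The Trial status section reports about half of the participants recruited, and the detailed analysis plan is still to be written, so this can be done before the outcome data are examined. No change to recruitment, assessments or the planned estimates is needed.
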